## Abstract

**Background:**

People with severe mental illness (SMI) face not only impaired mental health, but also a greater risk of physical comorbidities and a shorter life expectancy compared to the general population. A poor lifestyle plays a substantial role in this disparity. *Combined Lifestyle Interventions* targeting multiple lifestyle behaviors can improve mental and physical health, and quality of life. However, there is currently no appropriate structural support for people with SMI in outpatient care in the Netherlands. The *Combined Lifestyle Intervention for Outpatients with SMI (GOAL!)* is developed to address this gap. This study examines the (cost-)effectiveness and implementation of GOAL!.

**Methods:**

In a type 1 hybrid quasi-experimental study with a mixed-method matched design, GOAL! participants (*N* = 50) are compared to people receiving care as usual (*N* = 50). The GOAL! program includes group and individual sessions, given by allied health professionals, over a period of two years. The first year starts with a 3-month intensive course on physical activity and nutrition, followed by 9 months of aftercare covering various lifestyle topics tailored to the group’s needs. There is close collaboration with local stakeholders to facilitate transfer to the community setting. The second year focuses on maintaining established activities in one’s daily living environment. Our primary outcome will be the change in physical activity, comparing GOAL! participants to those receiving care as usual. Secondary outcomes are changes in other lifestyle behaviors, physical health, mental well-being, and healthcare and societal costs. Additionally, achieving lifestyle-related goals, adverse effects, and barriers and facilitators to implementation are examined. Measurements are obtained at start (T0), and after 3 (T1), 12 (T2) and 24 months (T3).

**Discussion:**

This study investigates the effects of GOAL! on lifestyle behaviors, health outcomes, implementation factors and cost-effectiveness after two years, aiming to offer valuable insights into the effectiveness and implementation outcomes of lifestyle interventions for outpatients with SMI.

**Trial registration:**

: ClinicalTrials.gov (Identifier: NCT05600205). Prospectively registered on October 26, 2022.

## Background

People with a severe mental illness (SMI) have a greater prevalence of physical conditions compared to the general population [1–3]. SMI mainly concerns people with psychotic, personality, and major mood disorders who require long-term care. They have up to two times higher risk of developing cardiometabolic diseases, irrespective of their diagnosis [4]. This multimorbidity leads to elevated healthcare utilization [2], a heightened risk of hospitalization [3], and a shorter life expectancy of up to 15 years compared to the general population [5–8]. In addition, people with multimorbidity have increased difficulties in daily living, psychiatric symptoms, and cognitive functioning [9]. The prevalence of this multimorbidity and reduced life expectancy appears to be increasing, highlighting the urgent need for targeted interventions to improve their overall health [5, 10–12].

Lifestyle behaviors play a substantial role in the health of people with SMI [4, 11, 13]. They often have unhealthy lifestyle behaviors, such as low physical activity levels, poor nutritional intake, disturbed sleeping patterns, and high smoking rates [13–18]. Because lifestyle behaviors are modifiable, there is great potential to improve the mental and physical health of people with SMI by targeting lifestyle changes within their treatment. Studies have shown that lifestyle interventions can improve not only lifestyle factors, such as physical activity [14, 19, 20], nutrition [21], sleep [15], and smoking cessation [18, 22], but also physical health [19, 23–25], mental health [19], psychosocial functioning, quality of life [23, 26], and medication use [27]. Long-term (i.e. longer than 12 months) multidisciplinary support focused on multiple lifestyle behaviors seems most effective for intervention success [4, 13]. Additionally, support should focus on both education and behavioral change [16]. The physical and social characteristics of community contexts in which people with SMI reside can also play an important role in promoting or hindering healthy lifestyle behaviors [28]. Interventions addressing the social determinants of health, such as reducing loneliness and isolation, and improving social participation (e.g., employment), may have the greatest potential to reduce early mortality [12]. In summary, long-term multidisciplinary interventions incorporating multiple lifestyle behaviors, behavioral strategies, and considering environmental factors holds promise for achieving sustainable improvements in the health and life expectancy of people with SMI.

There are existing lifestyle interventions that follow this perspective, but they are often inappropriate for people with SMI. In the Netherlands, the *Combined Lifestyle Interventions (CLIs)* target multiple lifestyle behaviors simultaneously and are reimbursed in the national health insurance scheme for everyone with (a high risk of) diabetes or obesity. These CLIs are based on effective *Diabetes Prevention Programs* [29, 30], which are also identified in the literature as the “gold standard” for people with SMI [4]. However, people with SMI are often excluded from CLIs because of their psychopathology, medication use, or lack of motivation [31, 32]. This highlights the lack of tailored support that addresses their increased challenges to lifestyle changes, such as illness-related symptoms, physical comorbidities, stress, and medication side effects [33–36]. For example, the direct and indirect side effects of medication can form a barrier through causing metabolic disturbance, body weight gain, movement disorders, and increased appetite [35, 37–40]. People with SMI, relatives and healthcare practitioners indicate the need for lifestyle interventions for people with SMI in outpatient care, who often lag behind public health progress [4, 13, 23].

To address this gap, the *Combined Lifestyle Intervention for Outpatients with SMI (GOAL!)* was developed. GOAL! provides multidisciplinary support from allied health professionals and peer support workers for two years. In this program, participants receive group-based and individual support on various lifestyle behaviors. GOAL! builds on effective components of existing CLIs, but is tailored to address the needs of people with SMI. The program was co-created with people with lived experience, relatives, peer support workers, healthcare practitioners, CLI experts, healthcare insurers, and community partners (e.g., policy makers of municipalities and community service providers). This resulted in a program with increased individualized support and guidance from professionals with expertise in mental healthcare and related challenges (e.g., medication side effects). To facilitate a personalized transfer to people’s own daily living environment, there is close collaboration with local stakeholders within the community setting, thereby aiming for sustainable lifestyle behavior change.

The aim of this study is to investigate the (cost-)effectiveness and implementation of GOAL!. This provides a comprehensive understanding of the effects of such a lifestyle intervention on lifestyle behaviors, physical health, mental well-being, and healthcare and societal costs in outpatients with SMI. By identifying barriers and facilitators to implementation, we gain insights into underlying mechanisms behind intervention success and failure. These results can inform decision making by stakeholders involved in the implementation of such support for people with SMI within outpatient care.

## Methods

### Design and setting

This is a type 1 hybrid quasi-experimental study with a mixed-method matched design. This design allows for the assessment of the effectiveness of GOAL! on health-related outcomes while collecting and analyzing implementation data [41]. An intervention group (*N* = 50) will be compared with a control group (*N* = 50) who continue to receive care as usual and are matched by demographic characteristics. GOAL! is designed in collaboration with stakeholders in multiple municipalities in the Netherlands where GOAL! will be implemented. To avoid contamination, the control group will be recruited in separate municipalities. Due to the nature of the intervention, and the innovative approach to care of this research, randomization or blinding is not possible. Measurements are obtained at start (T0), and after 3 (T1), 12 (T2), and 24 months (T3).

### Eligibility criteria

People are eligible to participate if they are 18 years or older, diagnosed with SMI, have an abdominal circumference of ≥ 102 cm for men or ≥ 88 cm for women, and have at least one of the other four risk criteria as clustered in the metabolic syndrome: hypertension (systolic ≥ 130 and/or diastolic ≥ 85 mmHg); abnormal triglycerides (≥ 1.7 mmol/l); fasting blood sugar (≥ 5.6 mmol/l); HDL cholesterol (< 1.0 mmol/l for men; <1.3 mmol/l for women); or pharmacological treatment for one of these. People are not eligible if they, or a legal representative, are unable to provide written informed consent, if addiction is the primary diagnosis, or if the severity of the disease does not allow participation at that time (e.g. acute psychosis or suicidality, in consultation with their relevant healthcare practitioner). Additionally, residents of the intervention region are eligible to participate in GOAL!, while residents of the control region are eligible to participate in the control group.

### Recruitment

GOAL! is promoted within mental health organizations in the intervention region through flyers, presentations, and introductory meetings. Healthcare practitioners invite eligible people to participate in GOAL!. Interested participants are referred to a lifestyle coach for an intake session. Upon enrollment, GOAL! participants are encouraged to voluntarily participate in the evaluation. If participants express interest, the lifestyle coach assists in establishing communication with the research team for potential inclusion. GOAL! participants who take part in the evaluation will receive gift vouchers of €5 at T0, €10 at T1, €15 at T2, and €30 at T3.

In collaboration with mental health organizations in the control region, eligible participants are invited by their healthcare practitioners to enroll in the control group. Healthcare practitioners will then facilitate communication for interested participants with the research team for potential inclusion. Participants of the control group will receive gift vouchers of €10 at T0, €20 at T1, €40 at T2, and €50 at T3.

### Sample size

The sample size calculation is based on changes in lifestyle behaviors and health outcomes, for which we used data from a previous study on inpatients in the Netherlands [19]. A sample size of 98 participants is necessary to detect an average effect (f^2^ = 0.15) in a linear regression analysis with 80% power, 95% confidence interval, and six variables in the model. After reaching consensus on feasibility with the collaborating region, it was decided to enroll 50 people to participate in the GOAL! program and recruit an equally sized control group.

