### Outcome measures

The primary outcome is the change in physical activity between participants of GOAL!, compared to participants who receive care as usual. Secondary outcomes focus on changes in other lifestyle behaviors, physical health, mental well-being, and healthcare and social costs. In addition, the achievement of lifestyle goals, adverse effects, and barriers and facilitators to implementation are examined. Implementation factors are also investigated among healthcare practitioners and stakeholders.

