### Statistical analysis

To assess the effect of GOAL! on lifestyle behaviors and health outcomes, data will be analyzed via multiple linear regressions and linear mixed models (LMMs). LMMs allow for testing the effect over time (four measurement points) and accounting for potential clustering (e.g., participant groups). In all analyses, the treatment condition (GOAL! participants vs. control group, coded as 1/0) will be the independent variable, and the outcomes measures will be the dependent variables, with physical activity (in minutes per week) as the primary outcome. All analyses will be adjusted for potential confounders, such as age (continuous), sex (male vs. female, coded as 0/1), key diagnostic subgroups (categorial, added as dummy variables), baseline values (continuous), session adherence (continuous), and changes in medication use (continuous).

When necessary, missing data will be addressed through multiple imputations via the MICE package in R. When constructing the imputation model, we will include the variables used as predictors in our analysis. The number of imputations and iterations will be based on the proportion of missing data in our LMM. Results from imputed datasets will be pooled using Rubin’s rules.

Implementation factors are processed according to the manual of the measurement instrument. Cost-effectiveness is analyzed in a health-technology assessment.

All analyses will be performed with IBM SPSS statistics 25 and R version 4.04 or higher, based on 95% confidence intervals (*p* < 0.05), and if necessary will be corrected for multiple outcomes (Bonferroni correction).

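### The 98 participants reproduce only as an overall test of all six regressors, so the stated 80% is not the power for GOAL! versus care as usual, and the error can go either way

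*Protocol article*

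**What the plan says.** The Sample size section of the protocol article states: "A sample size of 98 participants is necessary to detect an average effect (f^2^ = 0.15) in a linear regression analysis with 80% power". It completes the inputs with "95% confidence interval, and six variables in the model". It names neither the term to be tested nor whether f² describes the whole model or the treatment term alone. It then says that 50 per group was agreed with the collaborating region on grounds of feasibility, giving 100 in total.

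The trial's question is set elsewhere. Under Outcome measures: "The primary outcome is the change in physical activity between participants of GOAL!, compared to participants who receive care as usual". Under Statistical analysis: "the treatment condition (GOAL! participants vs. control group, coded as 1/0) will be the independent variable". The other model terms (age, sex, diagnosis, baseline value, session adherence, medication change) are introduced there as adjustment for confounding. The joint significance of all terms is nowhere made a hypothesis.

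**The concern.** In multiple regression, f² = 0.15 with six variables can feed two different power calculations. One tests whether the six variables jointly explain any variance (6 numerator df). The other tests whether one of them, here treatment, adds to the rest (1 df). Only the second answers the trial's question. The first can reject because baseline activity, age or diagnosis predicts the outcome, even if GOAL! does nothing.

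If 98 comes from the first test, the 80% attached to it is not the chance of detecting an effect of GOAL!. Readers will nevertheless take it that way. A null result could be read as excluding a medium-sized effect with 80% power, although the article never says which treatment effect the study can detect.

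**Working it through.** **Inputs.** From Sample size: N = 98, f² = 0.15, power 80%, six regressors. From Statistical analysis: "based on 95% confidence intervals (*p* < 0.05", so alpha = 0.05. Allocation is 1:1 (50 + 50).

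**Formula.** Noncentral F for fixed-effects regression: noncentrality λ = f² × N, numerator df u = number of terms tested, denominator df v = N − 6 − 1. Power is the probability that a noncentral F(u, v, λ) exceeds the central 95% point of F(u, v).

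**Step 1: reproduce the stated figure.** With u = 6, N = 98, v = 91 and λ = 0.15 × 98 = 14.7, power is 80.4%. At N = 97 it is 79.8%. The smallest N reaching 80% is therefore 98, an exact match.

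**Step 2: try the alternatives at f² = 0.15.**

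| Test | N for 80% power |
|---|---|
| 1 of 6 terms (treatment alone) | 55 |
| 2 of 6 | 68 |
| 3 of 6 | 77 |
| 4 of 6 | 85 |
| 5 of 6 | 92 |
| all 6 of 6 | **98** |
| overall test, 5 regressors | 92 |
| overall test, 7 regressors | 103 |
| overall test, 8 regressors | 109 |

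A one-sided test of the single coefficient gives 43. Only the overall six-term test gives 98.

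**Step 3: power for the treatment coefficient at N = 98 (u = 1, v = 91).**

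- *f² = 0.15 read as the partial effect of treatment.* Power is 96.7% (96.9% at N = 100), and 55 would be enough for 80%.
- *f² = 0.15 read as the whole-model effect.* Then R² = 0.15/1.15 = 0.130. With uncorrelated regressors, a treatment share s of the explained variance gives partial f² = s × 0.15. The shares below are assumed; the article gives none.

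| Share s | Partial f² | Power at 98 |
|---|---|---|
| 1/6 | 0.025 | 34% |
| 1/3 | 0.050 | 59% |
| 1/2 | 0.075 | 76% |
| 3/4 | 0.1125 | 91% |

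**Step 4: what the stated N can detect.** Solving for 80% power with u = 1 gives partial f² = 0.082 at N = 98 (0.080 at N = 100). That is 0.0818/0.15 = 54.5% of the stated f², so on the whole-model reading power falls below 80% only if treatment holds less than about 55% of the explained variance. With fewer analysed (assumed), the detectable partial f² rises to 0.101 at 80 and 0.116 at 70.

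**Step 5: in SD units.** With 1:1 allocation and treatment uncorrelated with the covariates, d = 2√f² = 2 × √0.0818 = 0.57 residual SD. If treatment has multiple correlation R with the covariates, this is multiplied by 1/√(1 − R²). For assumed R:

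- R = 0.5: 0.572/√0.75 = 0.66
- R = 0.7: 0.572/√0.51 = 0.80
- R = 0.8: 0.572/√0.36 = 0.95
- R = 0.9: 0.572/√0.19 = 1.31

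**The case against.** **The test is inferred.** The article never says it used an overall test, and the full protocol may define f² and the tested term. This stands as a limit on wording: the defensible statement is that 98 reproduces only as the overall test. It does not rescue the figure, because the article gives a complete set of inputs, and under them 98 is not the requirement for the treatment coefficient on either reading of f².

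**Harm is not shown.** A reader might infer that the trial is underpowered. The documents do not support that. On the partial reading the calculation is conservative (97%). On the whole-model reading the shortfall depends on a share that the article does not give, and a share of 3/4 yields 91%. One can also build a case with no GOAL! effect: a baseline-to-follow-up correlation of 0.36 alone supplies R² = 0.13, and in simulation the overall test then rejects about 79% of the time while the treatment test rejects at roughly its nominal rate (4% to 5%). That result follows by construction from an assumed correlation. It shows the principle and says nothing about this population.

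**A single SD figure would mislead.** A reader might take 0.57 residual SD as the detectable difference. It is a best case. Groups are formed by region without randomization, and the model adjusts for session adherence although the sessions belong to GOAL!, so treatment is unlikely to be uncorrelated with the covariates. This objection stands and limits the fix.

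**Consequence is limited.** The final 50 per group followed a feasibility agreement, and nothing in conduct changes. That is true, but the article still presents 98 as the statistical requirement.

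**Conclusion.** The point holds in this form. The 98 is exactly the size for an overall 6-df F test at f² = 0.15, and no other variant tried gives it. The trial tests a single 1/0 coefficient, so the stated 80% is not the power for GOAL! versus care as usual. The direction of the error is not fixed: 97% if f² = 0.15 is the partial effect of treatment, and about 34% to 91% for assumed treatment shares of 1/6 to 3/4 if it is the whole-model effect. The 80% applies to treatment only at a partial f² of about 0.082, a value the article does not state.

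The share figures assume uncorrelated regressors. All figures assume six regressors, 98 analysed and no clustering. What fails is the justification of the sample size; the documents do not establish that the sample is too small.

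**What to change.** Keep the sample size. Remove the claim that 98 is the number required for f² = 0.15, and restate the basis for the 1-df treatment coefficient, for example:

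> With 98 analysed participants and six regressors, the two-sided 5% test of the treatment coefficient has 80% power for a partial f² of 0.082, before loss to follow-up or clustering.

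If a difference in SD units is added, say that 0.57 residual SD is the best case, with treatment uncorrelated with the covariates, and that it grows by 1/√(1 − R²) of treatment on the covariates (for example 0.66 SD at R = 0.5 and 0.80 SD at R = 0.7, both assumed). Convert to minutes per week only if the earlier inpatient data provide a suitable SD; the article does not say that they do.

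The cost is one or two sentences in the protocol or analysis plan, with no extra participants and no change to the analysis.

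### The stated 80% power at 98 participants matches a joint test of all six regression coefficients, not the test of the treatment effect that is the primary question

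*Protocol article*

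**What the plan says.** The Sample size section of the protocol article gives 98 as the total required. The target is f² = 0.15, which the section calls average, and the setting is described as follows: "in a linear regression analysis with 80% power, 95% confidence interval, and six variables in the model". It cites an earlier inpatient study as the source but gives no difference or standard deviation for physical activity. It then sets enrolment after discussing feasibility with the region: "enroll 50 people to participate in the GOAL! program and recruit an equally sized control group", which is 100 in total.

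The Outcome measures section defines the primary question: "The primary outcome is the change in physical activity between participants of GOAL!, compared to participants who receive care as usual". The Statistical analysis section carries that question in one binary term: "the treatment condition (GOAL! participants vs. control group, coded as 1/0) will be the independent variable". The other variables enter as adjustment for confounding. The named ones are age, sex, diagnosis ("key diagnostic subgroups (categorial, added as dummy variables"), baseline value, session adherence and change in medication use. The significance level is 5% ("based on 95% confidence intervals (*p* < 0.05").

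**The concern.** In multiple regression, f² = 0.15 can describe two different things: the variance explained by the whole model, or the extra variance explained by one term after the others. They lead to different tests and different sample sizes. The Sample size section does not say which is meant, but the count of six variables affects the answer materially only under the first.

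The joint test is not a question that the trial asks. With the baseline value among the predictors, it could reject even if GOAL! had no effect at all, because earlier activity can be expected to predict later activity. A reader will nevertheless take the stated 80% as the power to detect a GOAL! effect on physical activity and will read the result, above all a null one, in that light. The protocol states no power for that effect.

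**Working it through.** **Inputs.** f² = 0.15, power 80%, six variables, N = 98 and enrolment of 50 + 50 = 100 (Sample size); α = 0.05 and a 1/0 treatment term (Statistical analysis).

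**Formula.** Power = P[F′(u, v, λ) > F₀.₉₅(u, v)], where F′ is the noncentral F, u is the number of coefficients tested, v = N − k − 1 with k predictors in the model, and λ = f² × N.

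**Step 1: reproduce 98.** For the joint test u = k = 6. At N = 98, v = 91, λ = 0.15 × 98 = 14.7 and the critical value is 2.20; power is 80.4%. At N = 97 power is 79.8%, so 98 is the smallest size that reaches 80%.

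**Step 2: try the alternatives.**

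| Test at f² = 0.15, 80% power | N required |
|---|---|
| Joint, 5 predictors | 92 |
| Joint, 6 predictors | **98** |
| Joint, 7 predictors | 103 |
| One coefficient, two-sided, 1 to 7 predictors | 55 |
| One coefficient, one-sided, 1 to 7 predictors | 43 |

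Only the joint test with six predictors gives 98.

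**Step 3: power of the treatment test (u = 1, k = 6, two-sided 5%).**

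*Reading A: 0.15 is the treatment's partial f².* The required size is 55 (power 80.4%; 79.6% at 54). At N = 100, λ = 15 and power is 96.9%.

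*Reading B: 0.15 belongs to the whole model.* Let treatment carry a share s of it and, as an assumption, be uncorrelated with the covariates. Its partial f² is then s × 0.15. The documents give no value for s, so a range is shown:

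| Assumed share s | Partial f² | Power at N = 100 |
|---|---|---|
| 3/4 | 0.1125 | 91% |
| 1/2 | 0.075 | 77% |
| 1/3 | 0.050 | 60% |
| 1/6 | 0.025 | 35% |

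The partial f² with exactly 80% power is 0.0818 at N = 98, so the break-even share is 0.0818 / 0.15 = 0.545, about 55%.

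**Step 4: what the enrolment supports.** With equal groups, the difference in residual SDs is 2√f².
- 100 analysed: 80% power at partial f² = 0.0801, and 2√0.0801 = 0.57 residual SDs.
- 80 analysed (an assumed 20% loss): partial f² = 0.1008, and 2√0.1008 = 0.63 residual SDs.

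**Step 5: the variable count.** Treatment plus the six named adjustment items makes at least seven terms, and more if diagnosis needs several dummies. For the 1-df test this is immaterial: at f² = 0.15 and N = 100, power is 96.94% with six predictors, 96.94% with seven and 96.94% with eight.

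**The case against.** The strongest reply is that the arithmetic is right and the trial may be amply powered. Both parts stand. The 98 reproduces exactly, so this is a mismatch between the hypothesis that was powered and the one that will be tested, not a calculation error. If the protocol's average effect is the treatment's partial effect, 100 participants give about 97% power, and 60 analysed would still give 84%. A reader might infer that the trial cannot reliably detect an average effect, but the documents do not support that. Treatment power is below 80% only under assumed shares of the model's f² that the protocol nowhere gives.

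A reader might also convert f² = 0.15 to 2√0.15 = 0.77 and call it an implausibly large group difference. That figure is in residual SDs, after adjustment that includes the baseline value. On the raw SD scale the same effect is smaller by an amount that depends on how much the covariates explain, which the documents do not say.

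A third tempting reading is that seven predictors require 103 participants, more than the 100 to be enrolled. That uses the joint test, which is the wrong test here, and the covariates are listed as examples, not as a fixed model. The shortfall disappears for the 1-df test.

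Finally, the protocol does not name its test, so the joint test is an inference. It rests on an exact match that none of the other variants tried shares.

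**Conclusion.** The point holds as a mismatch. The 80% power attached to 98 participants belongs to the joint 6-df test, and no power is stated for the treatment coefficient that answers the primary question. Neither reading rescues the paragraph: under Reading A, 98 is not the size that follows from the inputs (55 is); under Reading B, treatment power is unknown.

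It is not a finding that the trial is underpowered, nor that enrolment falls short. The figures assume a single regression at one time point, independent observations, equal groups and, for Reading B, treatment uncorrelated with the covariates. They do not model the mixed model over four measurement points, or any overlap between treatment and session adherence. The difference between six variables and the seven or more terms named in the Statistical analysis section is a minor inconsistency.

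**What to change.** Rewrite the sample-size paragraph for the 1-df treatment term, keep the enrolment of 50 + 50, and say that f² is the treatment's partial effect. Drop the statement that 98 gives 80% power for an average effect. Suggested text:

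*With 100 participants analysed, the covariate-adjusted treatment coefficient for physical activity has 80% power (two-sided 5%) for a partial f² of about 0.08, a difference of about 0.57 residual (covariate-adjusted) SDs. With 80 analysed, allowing for 20% loss, the corresponding values are about 0.10 and 0.63.*

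The 20% is an assumption, for the sponsor to replace with its own expectation; the Discussion itself warns of possible high dropout. State which time point or mixed-model contrast the figure refers to. If the sponsor holds a suitable SD, also give the difference in minutes per week; the article does not supply one. Because these values are worked back from a feasible sample size, add a sentence on whether a difference of that size is worth detecting.

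Separately, reconcile the six variables with the terms named in the Statistical analysis section.

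The cost is one rewritten paragraph. No participants are added, and neither the design nor the analysis changes.
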